### Interim analyses {21b}

A formal interim analysis is not planned. Since the ET is already an approved medical device for the indication stated in the study, it is not expected that serious safety-relevant events will be observed. Therefore, no data safety and monitoring committee will be established. The steering committee will decide on the extension of the planned recruitment period based on the recruitment figures.

### Methods in analysis to handle protocol nonadherence and any statistical methods to handle missing data {20c}

N/A, as protocol nonadherence and missing data are not expected as the intervention is performed by the endoscopist and the follow-up period is short (30 days).

### Plans to give access to the full protocol, participant level-data and statistical code {31c}

The full study protocol is planned to be published in an international PubMed-registered journal (e.g. Trials). The anonymized participant-level data will be publicly accessible in the BioStudies public repository [15] after completion of the study.

### Composition of the data monitoring committee, its role and reporting structure {21a}

N/A. A data monitoring committee is not planned, as there will be only one follow-up interview after 30 days asking about rebleeding.

### Adverse event reporting and harms {22}

Adverse events (AEs) will be documented at the start of oral endoscope insertion and will end 30 days after the first haemostatic procedure. The type and number of adverse events are secondary outcome variables as defined above. Subsequent adverse events may no longer be directly related to details of the study or procedure. Overall, adverse events attributable to ST or ET are expected to be rare [3, 9]. An adverse event is defined as a serious adverse event (SAE) if it is fatal, life-threatening, or results in permanent or severe disability or incapacity. If an adverse event is classified as serious, it will be documented on a separate SAE form in addition to the AE documentation in the CRF. Patients will be asked at the 30-day query if any adverse or serious adverse events occurred. Adverse events will be documented in the CRF with the following parameters: date and time of occurrence and cessation, association with trial therapy, and outcome of the adverse event. Conditions that existed prior to the administration of the investigational product will be documented not as adverse events but as concomitant conditions. Any new disease or any disease that increases in severity during the trial shall be documented as an adverse event. Each adverse event shall be assessed by the investigator as to whether a relationship to the intervention can be suspected. The nature and pattern of the reaction, the temporal relationship with the intervention, the clinical condition of the patient, concomitant medication, and other relevant clinical parameters should be considered. If the event occurs due to lack of efficacy or due to the underlying disease, it shall be considered independent.

The following definitions are used to assess the causality of the adverse event with the intervention (WHO Causality Assessment of Suspected Adverse Reactions) [16]:Certain: an event directly related to the intervention and observed, e.g. organ perforationProbable: an event that has a traceable temporal relationship to the use of the test therapy, e.g. a temporally displaced organ perforationPossible: an event that is reasonably temporally related to the use of the intervention but could easily have been caused by a number of other factors, e.g. a heart attackUnlikely: an event for which there is sufficient information to suggest that it is not related to the intervention, such as skin exanthemaNot assessed: an event reported as an adverse event for which no assessment of association was made at the time of reporting because further data are needed or are currently being collectedNot assessable: an assessment of the association is not possible

Regardless of the presumed causal relationship, each SAE must be documented and reported to the coordinating body. The PI, the steering committee, and the person responsible for SAE management jointly decide whether a report must be made to the medical device manufacturer and to the Federal Institute for Drugs and Medical Devices (BfArM).

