
### Objectives {7}

The efficacy and safety of bipolar haemostatic forceps should be investigated in the primary treatment of active, nonvariceal upper gastrointestinal haemorrhage of any cause (except tumour haemorrhage) in a randomized, prospective, multicentre superiority trial. In this setting, bipolar haemostatic forceps are the experimental study arm, and the standard therapy of haemoclip + / − epinephrine injection is the comparator study arm. The primary objective is the combined endpoint of successful initial endoscopic haemostasis and the absence of rebleeding within 30 days after successful initial haemostasis. Secondary objectives are the number of salvage procedures such as OTSC, angiography + coiling or surgery for primary haemostasis, type and number of therapy-associated complications, number of endoscopic reinterventions in 30-day intervals, number of blood units transfused, length of hospital stay, length of intensive care unit stay, and 30-day mortality.

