### Sample size {14}

The study hypothesis is that experimental therapy is superior to standard therapy in terms of clinical success, defined as successful haemostasis and no (signs of) rebleeding within 30 days. In one study, the rates of successful haemostasis and rebleeding in the experimental group were 92.3% and 0%, respectively [9]. However, this nonrandomized trial also included nonactive nonvariceal bleeding. Therefore, the rate of successful haemostasis could be lower and the rate of rebleeding higher when only active nonvariceal bleeding is present. Therefore, a success rate of 90% for primary haemostasis and a rebleeding rate of 5% were assumed, giving a combined clinical success rate of 85.5%. In a recently published study comparing the Over-the-Scope Clip (OTSC) with the haemoclip in high-risk patients with acute nonvariceal upper gastrointestinal bleeding, the rates of successful haemostasis and rebleeding in the standard of care arm (haemoclip only) were 73.1% and 15.4%, respectively [12]. However, this randomized trial also included nonactive, nonvariceal bleeding. Therefore, the rate of successful haemostasis could be lower and the rate of rebleeding higher if only active nonvariceal bleeding is present. Therefore, a success rate of 72% for primary haemostasis and a rebleeding rate of 16% were assumed, resulting in a combined clinical success rate of 60.1%. Power analysis of the combined primary endpoint revealed that 45 patients per treatment arm are required to demonstrate an absolute difference of 25.4 percentage points (85.5–60.1%) with a power of 80% and a significance level of 0.05. Here, a simulation-based line calculation assuming the above absolute differences was performed using the SimEngine package version 1.1.0, implemented in R version 3.3.0. Overall, a dropout rate of a maximum of 10% is assumed, as the follow-up period is only 30 days. A decision on the recruitment of follow-up patients will be made when 90 patients have been included as planned and the follow-up observations are available.

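### Non-fatal complications of failed haemostasis fall outside the only adverse event outcome, because events due to lack of efficacy or underlying disease are classed as independent and only therapy-associated events are counted

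*Protocol article*

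**What the plan says.** Objectives {7} names as the secondary safety objective the "type and number of therapy-associated complications". The list under Secondary and other outcomes in Outcomes {12} carries the same restriction: its one adverse event item covers therapy-associated events over 30 days. Adverse event reporting and harms {22} refers back to that list: "The type and number of adverse events are secondary outcome variables as defined above".

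The same harms section assigns the causality judgement: "Each adverse event shall be assessed by the investigator as to whether a relationship to the intervention can be suspected". It then fixes the answer for one class of events: "If the event occurs due to lack of efficacy or due to the underlying disease, it shall be considered independent". The causality scale that follows has six levels: certain, probable, possible, unlikely, not assessed and not assessable. None is called independent.

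On reporting, the section adds: "Regardless of the presumed causal relationship, each SAE must be documented and reported to the coordinating body". Who will be blinded {17a} leaves the endoscopist and the ward physicians unblinded. It says that outcome assessors are blinded, but not that they judge causality.

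**The concern.** In a haemostasis trial, much of the harm a poor method can do comes from bleeding it did not stop. The rule and the outcome definition together take those complications out of the adverse event count. The exclusion depends on efficacy, which is what the trial assumes differs between the arms, so it need not fall evenly. The less effective arm has more of its complications set aside and can look safer on this outcome than it is. Whether an event counts also depends on deciding if the device or the bleed caused it, and the text does not place that decision with a blinded person.

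**Working it through.** **Step 1: how an event leaves the outcome.**

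- Outcomes {12}: an adverse event counts only if it is therapy-associated.
- Harms {22}: an event due to lack of efficacy or to the underlying disease must be called independent.
- Consequence: a non-fatal complication of continued bleeding is recorded as an adverse event but is not counted in the adverse event outcome.
- The harms section's restatement of the outcome omits the restriction to therapy-associated events. It points back to the earlier definition, however, which contains it. It therefore does not clearly restore an all-event count.

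**Step 2: the plan's own figures (Sample size {14}).** The assumed rates are:

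- ET: primary haemostasis 90%, rebleeding 5%. 0.90 × 0.95 = 0.855, which matches the stated 85.5%.
- ST: primary haemostasis 72%, rebleeding 16%. 0.72 × 0.84 = 0.6048, against the stated 60.1%. The gap is small; both values are carried below.
- 45 per arm: with the stated 85.5% and 60.1%, two-sided 0.05, 80% power and unpooled variance, (0.855 × 0.145 + 0.601 × 0.399) × (1.960 + 0.842)² / 0.254² = 44.3, rounded up to 45. The plan's number is reproduced, and 45 is used as the arm size.

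**Step 3: expected failures per arm of 45.**

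| | ST | ET | Ratio |
|---|---|---|---|
| Primary haemostasis fails | 28%: 12.6 | 10%: 4.5 | 2.8 |
| Failure or rebleeding, exact product | 1 − 0.6048 = 39.5%: 17.8 | 1 − 0.855 = 14.5%: 6.5 | 2.73 |
| Failure or rebleeding, stated 60.1% | 39.9%: 18.0 | 14.5%: 6.5 | 2.75 |

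These are ratios of failures, not of harms.

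**Step 4: from failures to excluded events.** The article gives no rate of complications after failure. Let q be the share of patients with failure or rebleeding who have a non-fatal complication of it, equal in both arms. Both the equality and the range of q are assumptions. Excluded patients per arm are 45 × failure rate × q, using the exact product for ST.

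| q | ST excluded | ET excluded | Difference |
|---|---|---|---|
| 10% | 1.8 | 0.7 | 1.1 |
| 25% | 4.4 | 1.6 | 2.8 |
| 50% | 8.9 | 3.3 | 5.6 |

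For the exclusion to fall equally on both arms, harm per failure in ET would have to be 0.3952 / 0.145 = 2.73 times that in ST.

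**The case against.** The strongest reply is that nothing is lost. Every new or worsening disease is documented as an adverse event, every serious event is reported whatever its cause, deaths are counted from any cause, and crossover, rescue, reintervention, transfusion, hospital stay and intensive care stay are outcomes in their own right. Failure and rebleeding form the primary endpoint. Separating device injury from lack of efficacy is a common convention, and the stated objective is therapy-associated complications, which is what the outcome counts.

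Much of this stands. A reader might infer that the harms of failed haemostasis vanish from the trial, or that it cannot address safety at all. The documents do not support either: the exclusion affects one secondary count, and fatal bleeding is captured by 30-day mortality. What remains is that the other outcomes measure death and resource use, not complications such as cardiac ischaemia, and the one outcome that would show these by arm filters them out.

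Four further inferences should be resisted.

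- The plan does not say that harms are almost three times as common under ST. It gives failure rates only.
- Aspiration during a crossover attempt is not excluded by rule. It arises during a study procedure and could be judged related.
- The scale's example of a heart attack as possibly related does not squarely contradict the independence rule. The former describes an event with several candidate causes, the latter one already attributed to failure or disease.
- The text does not establish that causality is judged unblinded. The investigator judges, outcome assessors are said to be blinded, and the link between the two is left open.

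It may also be said that an analysis plan, not shown here, could add an all-event table. That is possible, but the outcome definition and the independence rule are fixed in this article and would still need to be reconciled with it.

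**Conclusion.** The concern holds in limited form. As written, non-fatal complications of failed haemostasis drop out of the by-arm adverse event comparison, through an attribution given to the investigator and onto a scale with no level for it. Expected failure or rebleeding is 17.8 of 45 under ST and 6.5 of 45 under ET. If harm per failure is similar in the two arms, more events are set aside in the less effective arm: 1.1 to 5.6 more patients in ST for an assumed complication share of 10% to 50%. On the plan's rates that works against the forceps; if the forceps proved the less effective method, it would work in their favour. The direction rests on similar harm per failure, and the size rests on a share that the documents do not give. The primary endpoint and the sample size are unaffected.

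**What to change.** In Outcomes {12}, define the adverse event outcome as all adverse events and all serious adverse events to day 30, by arm, regardless of causality. Keep therapy-associated events as a supportive table, since they still answer the narrower question of device injury.

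In Adverse event reporting and harms {22}, replace the instruction to treat events as independent with a separate recorded category for events due to lack of efficacy or to the underlying disease, and add that category to the causality scale. Striking out only the reference to lack of efficacy would not be enough: shock or ischaemia from the bleeding lesion could still be set aside as underlying disease.

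The cost is wording in two sections, one extra table, and more background noise in the all-cause counts. Each adverse event is already documented with its association to therapy, so no new data collection is needed.

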### Frequency and plans for auditing trial conduct {23}

N/A, as both interventions are approved procedures or medical devices.

### Plans for communicating important protocol amendments to relevant parties (e.g. trial participants, ethical committees) {25}

Important protocol modifications will be communicated to the relevant parties of the multicentre study (e.g. investigators and trial participants), and an amendment will be requested from the relevant ethical committee.

### Dissemination plans {31a}

Within 1 year after completion of the clinical trial, the summary of the final report on the clinical trial, which includes all significant events of the study, will be submitted to the responsible ethics committee. It is planned to present the results of the clinical trial in a PubMed-listed scientific journal and/or at German and international congresses after consultation with the sponsor (Helios Kliniken Schwerin), the PI, and all investigators of the study centres. In principle, publication of the entire clinical trial is preferred. The “Uniform Requirements for Manuscripts Submitted to Biomedical Journals [17]” will be considered. There is no restriction on the publication of the study results.

## Discussion

The hypothesis of the study is that bipolar haemostatic forceps are superior to standard therapy with haemoclip + / − epinephrine injection in terms of successful primary haemostasis and the absence of recurrent bleeding within 30 days (combined endpoint). In a nonrandomized Japanese trial, the rate of successful primary haemostasis was 92.3%, and the rate of recurrent bleeding was 0% for bipolar haemostasis forceps [9]. However, active, nonvariceal bleeding was not considered in this study. Accordingly, successful primary haemostasis is expected to be somewhat lower and recurrent bleeding rates somewhat higher, as the method was used exclusively for active, nonvariceal bleeding in the BeBop study. In contrast, the rates of successful haemostasis and recurrent bleeding with standard therapy were 73.1% and 15.4%, respectively, in a recently published study in which the over-the-scope clip (OTSC) was the experimental arm [3]. This study also included nonactive, nonvariceal bleeding, so successful primary haemostasis may be lower and repeat bleeding rates higher when treating active, nonvariceal bleeding. The expected difference in success rate between the two procedures with respect to the combined endpoint was therefore calculated to be 25.4%, which is the basis for the case number calculation (*n* = 90). The 1:1 randomization is also ethically justifiable for this study, as both procedures are approved for the intervention in question. To further increase the safety of the patients in the study, crossover treatment and rescue treatment are planned. The prospective design seems feasible in a reasonable time frame (recruitment period of 12 months), as nonvariceal upper gastrointestinal bleeding is common [1]. Therapy with anticoagulants, antiplatelet agents, or a combination of the two is often associated with gastrointestinal bleeding [18, 19]. Therefore, anticoagulants and/or antiplatelet drugs could be an important confounding factor in the statistical analysis that needs to be considered and calculated if necessary [20]. Tumour haemorrhage is usually accompanied by diffuse bleeding at several sites and haemostasis by clip or haemostatic forceps did not appear to be promising. Therefore, tumour haemorrhage was not included in the study as it could bias the statistical results. In consequence, this study cannot make a reliable statement about the use of haemostasis forceps in terms of haemostasis of tumour bleeding in the upper gastrointestinal tract. In conclusion, this randomized, prospective, multicentre study could make an important contribution to answering the question of whether bipolar haemostatic forceps could be the first-line therapy in the endoscopic treatment of upper gastrointestinal nonvariceal bleeding stage Forrest I a + b.

## Trial status

Study protocol version 2.3 from 19 December 2022 is the currently valid version. The following is the study timeline:Duration of clinical phase: [12 months]FSI (first subject in): [01 January 2023]LSI (last subject in): [31 December 2023]LSO (last subject out): [31 January 2024]DBL (database lock): [31 March 2024]Completion of the statistical analysis: [31 May 2024]Completion of the study report: [31 July 2024]

## Data Availability

All study data are made available on the BioStudies public repository [15]. There are no contractual agreements restricting the investigators’ access to the study data.

## Abbreviations

BfArM: Bundesinstitut für Arzneimittel und Medizinprodukte
CRF: Case report form
DS-GVO: Datenschutz-Grundverordnung (= German Data Protection Regulation)
EMR: Endoscopic mucosal resection
ESD: Endoscopic submucosal resection
ESGE: European Society of Gastrointestinal Endoscopy
DBL: Database lock
ET: Experimental therapy
FSI: First subject in
GRADE: Grading of recommendations, assessment, development, and evaluation
ICH-GCP: International Conference on Harmonisation-Good Clinical Practice
ICU: Intensive care unit
LSI: Last subject in
LSO: Last subject out
OTSC: Over-the-scope clip
PI: Principal investigator
POEM: Peroral endoscopic myotomy
NVUGIB: Nonvariceal upper gastrointestinal bleeding
SAE: Severe adverse event
SC: Steering committee
SOP: Standard operation procedure
ST: Standard therapy
